## Abstract

**Introduction:**

Multiple sclerosis (MS) is a demyelinating disease of the central nervous system with an underlying immune-mediated and inflammatory pathogenesis. Innate immunity, in addition to the adaptive immune system, plays a relevant role in MS pathogenesis. It represents the immediate non-specific defense against infections through the intrinsic effector mechanism “immunothrombosis” linking inflammation and coagulation. Moreover, decreased cerebral blood volume (CBV), cerebral blood flow (CBF), and prolonged mean transit time (MTT) have been widely demonstrated by MRI in MS patients. We hypothesized that coagulation/complement and platelet activation during MS relapse, likely during viral infections, could be related to CBF decrease. Our specific aims are to evaluate whether there are differences in serum/plasma levels of coagulation/complement factors between relapsing-remitting (RR) MS patients (RRMS) in relapse and those in remission and healthy controls as well as to assess whether brain hemodynamic changes detected by MRI occur in relapse compared with remission. This will allow us to correlate coagulation status with perfusion and demographic/clinical features in MS patients.

**Materials and Methods:**

This is a multi-center, prospective, controlled study. RRMS patients (1° group: 30 patients in relapse; 2° group: 30 patients in remission) and age/sex-matched controls (3° group: 30 subjects) will be enrolled in the study. Patients and controls will be tested for either coagulation/complement (C3, C4, C4a, C9, PT, aPTT, fibrinogen, factor II, VIII, and X, D-dimer, antithrombin, protein C, protein S, von-Willebrand factor), soluble markers of endothelial damage (thrombomodulin, Endothelial Protein C Receptor), antiphospholipid antibodies, lupus anticoagulant, complete blood count, viral serological assays, or microRNA microarray. Patients will undergo dynamic susceptibility contrast-enhanced MRI using a 3.0-T scanner to evaluate CBF, CBV, MTT, lesion number, and volume.

**Statistical Analysis:**

ANOVA and unpaired t-tests will be used. The level of significance was set at p ≤ 0.05.

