### Selection of Subjects

Subjects of both genders will be recruited in two centers: the Multiple Sclerosis Center of the Sapienza University of Rome and the Multiple Sclerosis Center of the IRCCS Regina Elena National Cancer Institute. The planned recruitment period will be of three years.

Prior to enrollment, all participants will be screened to check their inclusion and exclusion criteria.

Patient inclusion criteria will be:

Patients diagnosed with relapsing-remitting MS (93)Patients untreated or treated with only immunomodulatory therapy18–60 years old

Patient exclusion criteria will be:

pregnancyco-existing neoplastic, hematologic, thyroid, metabolic, thrombotic, or autoimmune diseasesdrug or alcohol addictedtherapy with immunosuppressive drugs, steroids, or any medication interfering with coagulation

We will evaluate 3 groups of subjects: 30 RRMS patients in relapse (Group I); 30 RRMS patients in remission, i.e., without relapse in the previous 2 months (Group II), and 30 sex- and age-matched healthy controls (Group III).

A relapse or exacerbation or “attack” was defined by the multiple sclerosis guidelines as a manifestation of new or worsened neurological symptoms lasting for more than 24 hours (94). Symptoms should be supported by subjective description and by objective clinical assessment with no other explanation for them. The relapse is separated from the previous “attack” by at least 30 days and usually persists for days or weeks, then slowly improves over weeks or a few months ending with partial or complete recovery, i.e., remission. MRI showed the new and/or active lesions in the majority of patients, and steroid therapy often accelerates the recovery of symptoms.

Relapse needs to be distinguished from a pseudo-exacerbation, which is defined as a temporary worsening of pre-existing symptoms without new MS-related neuroinflammation, thus an MRI does not detect active or new lesions (95). The causes of pseudo-relapses could be different and include infections with or without fever, increased body temperature due to over-exercising, sauna, hot shower/bath or weather, dehydration, hormonal changes during menstruation or severe psychological stress, surgery, trauma, medications, alcohol overuse, and several medical conditions as thyroid or other metabolic disorders. Pseudo-relapses usually last less than 24 hours and resolve after removing their triggering causes with no need for steroid therapy.

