### Data Analysis

#### Sample Size Calculation

Overall 90 subjects (30 for each group) will be enrolled to compare the level of complement C4a (55). By using the ANOVA test, this sample size will allow detection of effect size values [delta=(miA–miB)/sigma] equal to at least 0.71, with a statistical power of 80%, to a level of significance of 5%.

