#### Statistical Methods

Descriptive statistics will be used to summarize pertinent study information. Correlations between quantitative variables will be assessed with the Pearson r correlation. The associations will be analyzed by the Fisher exact test or Chi Square test for trends. Comparisons between disease subgroups and control group will be carried out for different variables, using either Student’s *t-*test or analysis of variance (ANOVA). If the ANOVA shows a statistical difference between subgroups, a post-hoc analysis with Bonferroni correction for multiple comparisons will be performed. For non-normally distributed data, non-parametric (Mann Whitney-U or Kruskal-Wallis-H) tests will be used. The level of significance is set at p ≤ 0.05 (SPSS version 20.0, SPSS Inc., Chicago, Illinois, USA).

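### Controls are matched on age and sex, but the tests named against them ignore both factors; if age and sex explain marker variance, those tests are conservative and forgo precision

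*Protocol article*

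**What the plan says.** Matching is stated twice. The Abstract (Materials and Methods) has "age/sex-matched controls (3° group: 30 subjects", and Selection of Subjects has "30 sex- and age-matched healthy controls (Group III". Neither place describes pairs, triplets or a matching ratio. One pool of 30 controls serves two patient groups of 30.

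The Abstract (Statistical Analysis) says "ANOVA and unpaired t-tests will be used". Statistical Methods says "Comparisons between disease subgroups and control group will be carried out for different variables", using Student's t-test or ANOVA, with Bonferroni-corrected post-hoc comparisons after a significant ANOVA. Its fallback is also for independent groups: "For non-normally distributed data, non-parametric (Mann Whitney-U or Kruskal-Wallis-H) tests will be used". Sample Size Calculation plans on an ordinary ANOVA: "Overall 90 subjects (30 for each group) will be enrolled to compare the level of complement C4a", with a detectable difference of 0.71 SD at 80% power and 5% significance.

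The primary outcomes are ten markers in RRMS patients and healthy people. In the analysis, age and gender appear only under Additional secondary outcomes, as correlates within the patient groups. No test named against controls uses them.

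**The concern.** When controls are chosen to resemble the patients on age and sex, those factors are balanced by design, and their contribution to a marker largely drops out of the difference in group means. An unadjusted t-test or one-way ANOVA still counts that contribution as error. The standard error is then larger than the true variability of the difference, so the test rejects less often than its nominal 5% and has less power than an analysis that uses the matching factors.

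The comparison with controls is the primary outcome, with 30 per group and a Bonferroni step to follow. Precision that the recruitment effort has already bought would be worth keeping.

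**Working it through.** **Inputs.** From the protocol: n = 30 per group, three groups, difference 0.71 SD, 5% significance (Sample Size Calculation); Bonferroni post-hoc comparisons (Statistical Methods). Not given, so assumed over a range: R², the share of marker variance explained by age and sex, at 0, 0.1, 0.2 and 0.3.

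**Step 1: the plan's own figure.** Take one group mean differing by 0.71 SD from two equal means. The noncentrality is 30 × (2/3) × 0.71² = 10.08 on 2 and 87 degrees of freedom. Power is 80.4% and the minimum detectable difference is 0.706 SD. The stated 0.71 at 80% therefore reproduces with independent groups and no credit for matching.

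For a single pairwise contrast, the noncentrality is 0.71 × √(30/2) = 2.75. Two-sided power is 77.2% on 58 degrees of freedom, or 77.6% with the ANOVA error term on 87. At 0.05/3 it is about 62% (87 degrees of freedom).

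**Step 2: what ignoring the factors does.** With age and sex balanced, the true variance of the difference in means is about 2σ²(1 − R²)/30, while the unpaired test estimates 2σ²/30. Its critical value is therefore effectively 2.002/√(1 − R²) instead of 2.002. An age/sex-adjusted contrast keeps the proper critical value, and its standardised difference becomes 0.71/√(1 − R²), on 87 − 2 = 85 degrees of freedom.

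| Assumed R² | Effective critical value, unpaired t | Actual size | Unpaired power | Adjusted power | Gain (points) |
|---|---|---|---|---|---|
| 0 | 2.002 | 5.0% | 77.2% | 77.6% | 0.4 |
| 0.1 | 2.110 | 3.9% | 78.3% | 81.7% | 3.4 |
| 0.2 | 2.238 | 2.9% | 79.6% | 86.0% | 6.4 |
| 0.3 | 2.393 | 2.0% | 81.1% | 90.1% | 9.0 |

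The 0.4 points at R² 0 come only from using the three-group error term. They are not a gain from age and sex.

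**Step 3: does this need individual pairs?** No. Frequency matching was simulated without any pairing: 30 versus 30, sex by four age bands over 18 to 60 years, 20,000 trials per setting.

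| Assumed R² | Size, unpaired t | Unpaired power | Adjusted power | Change (points) |
|---|---|---|---|---|
| 0 | 4.6% | 77.5% | 77.3% | −0.2 |
| 0.1 | 4.0% | 78.4% | 81.4% | 3.0 |
| 0.2 | 3.0% | 79.4% | 85.4% | 6.0 |
| 0.3 | 2.1% | 81.7% | 90.3% | 8.6 |

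The adjusted test kept a size between 4.7% and 5.1% throughout.

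**Step 4: the overall F test.** Adjusted for age and sex, its power at 0.71 SD is 80.4% at R² 0, 84.6% at 0.1, 88.8% at 0.2 and 92.6% at 0.3. It does not fall below the planned 80% at any of these values.

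**Step 5: would strict pairing be a safe alternative?** For 30 pairs with within-pair correlation ρ, the paired t-test against the unpaired t-test has power 75.7% v 77.1% at ρ = 0, 77.8% v 77.7% at 0.05, 80.0% v 78.3% at 0.1 and 88.8% v 81.1% at 0.3. Pairing loses slightly at zero correlation and breaks even near 0.05.

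**The case against.** The case on the other side is substantial, and most of it stands.

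- **No pairs are described.** Thirty controls cannot be paired one to one with 60 patients, and nothing says that relapse patients are matched to remission patients. A reader might infer that paired or blocked tests were required and that the plan misses them. The text does not support this; it fits group-level matching. Large gains computed for matched triplets at a high correlation, such as 0.5, do not apply to the design as written.
- **The effect is conditional.** A reader might infer that p-values against controls are certainly too large. That depends on an R² the documents do not give. At R² 0 there is nothing to gain, and at 0.1 the gain is about 3 points.
- **The error is in the safe direction.** With positive R² the named tests stay below 5%. No false-positive problem arises, and the planned power is met.
- **The quoted sentence is not wrong in itself.** It does not tie the unpaired t-test to the control comparison. Relapse versus remission is unmatched, and the perfusion and lesion outcomes compare only those two groups.
- **Detail may sit elsewhere.** The matching method and covariates could be in a fuller protocol or analysis plan that is not shown.

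The last point has limits. The article does more than stay silent: it names the tests for comparisons with controls, and none of them uses age or sex. Nor does frequency matching remove the issue, because the simulation without pairs shows the same loss of size and power.

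**Conclusion.** The point holds in a conditional form. Controls are matched on age and sex, and the tests named against them do not use those factors. If age and sex explain 10%, 20% or 30% of marker variance, the pairwise comparison forgoes about 3, 6 or 9 points of power at 0.71 SD and runs at an actual size of about 4%, 3% or 2%. If they explain none, nothing is lost. These figures rest on an assumed R², normally distributed markers with equal variance, and good balance on age and sex.

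A reader might go further and conclude that the sample size is wrong or the study underpowered against its own plan. The documents do not support that: 0.71 SD at 80% reproduces for the overall F test. What is forgone is extra precision beyond the plan. That matters most for the Bonferroni-level contrasts, where pairwise power without any gain from age and sex is about 62%. The change is worth making because it is cheap and safe, but the plan's tests do not produce false positives.

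**What to change.** In the Abstract (Statistical Analysis) and in Statistical Methods, specify that marker comparisons with Group III use a linear model with group, age and sex, with markers transformed or ranked where non-normal. Take the Bonferroni-corrected pairwise contrasts from that model. Keep the unpaired t-test as an acceptable choice for relapse versus remission. State whether matching is individual or by frequency; paired or blocked tests would be an option only if controls are in fact individually matched.

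The cost is a change of wording and 2 of 87 residual degrees of freedom. Age and sex are already needed to select the controls. If they explain nothing, the power loss is negligible: about 0.2 points in the simulation (77.5% v 77.3%). The sample size need not change.

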**Discussion:**

Identifying a link between activation of coagulation/complement system and cerebral hypoperfusion could improve the identification of novel molecular and/or imaging biomarkers and targets, leading to the development of new effective therapeutic strategies in MS.

**Clinical Trial Registration:**

Clinicaltrials.gov, identifier NCT04380220.

## Introduction

Multiple sclerosis (MS) is a chronic demyelinating and degenerative disease of the central nervous system (CNS) with an underlying immune-mediated and inflammatory pathogenesis (1). For many years, self-reactive T cells have been considered to have an exclusive role in the pathogenesis of MS, mainly due to findings from animal disease models such as that on experimental autoimmune encephalomyelitis (EAE) (2). Recent evidence has pointed out the crucial role of both B cells and innate immunity (3–6). In particular, it is hypothesized that innate immunity, which can be considered the immediate non-specific defense against any *noxa patogena* including infections and dangerous agents, not only stimulates and modulates adaptive immunity at MS onset but also mediates its neurodegenerative progressive phase (5, 6). Both inflammation and coagulation are the main effector processes of innate immunity acting synergistically through mutual regulation (7–10). Unlike what is commonly thought, direct and functional vascular injury, such as that caused by hypoxia, sepsis, malignancy, and inflammation, can activate coagulation (11, 12). Thus, thrombosis represents a physiological process in some conditions, “immunothrombosis,” an intrinsic effector mechanism of innate immunity (13). Immunothrombosis is aimed at recognizing the pathogens and counteracting their tissue invasion, dissemination, or survival, and it should be limited to only a restricted microvascular area to ensure sufficient overall organ perfusion. It is activated by blood-borne pathogens as well as by circulating self-components that are altered, and through its action on a platform consisting of fibrin, monocytes, neutrophils, and dendritic cells lead to fibrin formation and platelet activation.

In fact, many decades ago a relevant role of both coagulation and vascular thrombosis was hypothesized in MS (14). Subsequently, a number of studies focused on the role of either thrombin, fibrin(ogen), or other coagulation factors in MS due to the findings of both a close association between perivascular fibrin(ogen) deposition and clinical manifestations in EAE and its prompt improvement after the inhibition of thrombin generation by heparin and several anticoagulant agents (15). The discovery of some clotting factors in chronic active MS lesions by a proteomic approach has further strengthened this line of investigation (16).

Fibrinogen, produced by hepatocytes and cleaved off by thrombin, is an acute-phase reactant that increases during the inflammatory response and leads to the formation of insoluble and stable fibrin facilitating the formation of a platelet plug (17–19). In a recent study, high plasma fibrinogen levels resulted in a high specificity but a low sensitivity for detection of active lesions on MRI during relapses, suggesting a role of fibrinogen in the development of MS lesions (20). Moreover, fibrinogen transcripts were found to be present in chronic lesions of MS patients (21). Fibrinogen directly activated microglia *in vitro* and increased its phagocytic ability (22). Fibrinogen also induced the release of reactive oxygen species (ROS) in microglia, necessary for the formation of perivascular microglial clusters and axonal damage in EAE (23), stimulating the production of both tissue factor (TF) (24) and tumor necrosis factor (25) by monocytes. The conversion of fibrinogen to insoluble fibrin is fundamental for the binding of fibrin to the integrin receptor CD11b/CD18 expressed by microglia (18), leading to an increase of several cytokines that modulate cell adhesion and migration (26). Fibrin deposition in MS may precede and coincide with the formation of demyelinating lesions (27, 28) and with the area of axonal damage (29). In fact, a little deposition of extravascular fibrin has been observed in chronic, non-active MS lesions as a consequence of persistent blood-brain barrier (BBB) damage (28). Finally, fibrin-targeting monoclonal antibody immunotherapy could inhibit autoimmunity without suppressing innate immunity or interfering with coagulation (30).

Furthermore, significantly higher plasma levels of prothrombin and factor X have been found in relapsing-remitting (RR) MS (31). Of note, relapse-free time negatively correlated with levels of prothrombin, factor XII, or factor X, indicating that disease exacerbation is characterized by increased coagulation activity (31). Interestingly, the speed of thrombin generation was higher in relapsing-remitting than in primary progressive MS or healthy controls and correlated with time from clinical diagnosis, likely suggesting a differential active proinflammatory state in each MS subtype (32). By the proteomics approach, some serum proteins such as anti-thrombin, ceruloplasmin, clusterin, apolipoprotein E, and complement C3 were differently expressed in RRMS patients compared to controls (33). Besides, anti-thrombin was oxidatively modified in relapse compared with remission.

Protein C (PC) is a vitamin K–dependent zymogen of a serine protease activated by thrombin when both bind to endothelial cell thrombomodulin (TM) (34). PC also binds to the endothelial protein C receptor (EPCR). Activated PC (APC) is a natural anticoagulant and with its cell membrane localizing cofactor, protein S (PS), binds to both endothelium and activated platelet membranes and interferes with the degradation of procoagulant factor Va and VIIIa, thus limiting further thrombin formation. Recombinant TM ameliorated EAE clinically and pathologically by suppressing plasma levels of inflammatory cytokines (35).

Moreover, APC contributes to endothelial cell integrity (36), inhibits leukocyte adhesion and BBB crossing (37), reduces the production of pro-inflammatory cytokines (36, 38–41), and has anti-oxidant properties (42). A potential role of APC in MS pathogenesis has been hypothesized (43) since it was found reduced in MS patients regardless of their lupus-anticoagulant (LA) activity or factor Va resistance (44).

There are conflicting results in MS regarding the role of antiphospholipid antibodies (APLs), markers of increased coagulation activity, mostly due to methodological issues and to the type of antibodies used in the assays (45). Recently, a consensus has been reached among experts that APL reactivity is higher in MS than in healthy controls. However, this finding could be variable depending on the different disease forms and phases. In particular, a higher APL reactivity appeared to be associated with a more severe clinical and MRI disease progression (46), and with clinical exacerbations, sometimes followed by its decrease in the next months after the relapse (47–50). These thrombogenic mechanisms seem to correlate with neurodegenerative processes (51) enough to consider APLs as a new attractive therapeutic target in MS for use, for example, of hydroxychloroquine, an anti-infective, anti-inflammatory, and anti-thrombotic drug with specific protective property for annexin-V anticoagulant shield (52).

There are a number of studies confirming the involvement of complement in the pathogenesis of MS, highlighting its important role due to interrelation with coagulation as well as with both innate and adaptive immunity (53–57). Its components have been proposed as biomarkers of both MS disease activity and patient therapeutic response.

Ingram and collaborators have demonstrated augmented plasma levels of either C3, C4, C4a components, C1 inhibitor, or factor H as well as reduced levels of C9 in MS patients compared with controls (55). Based on the correlations between their plasma and cerebrospinal concentrations, synthesis of these components was suggested to be localized both systemically and intrathecally. A derived statistical model combined this complement profiling with patient demographic data reaching a predictive value of 97% for MS diagnosis and 73% for clinical exacerbation.

Moreover, an immunohistochemical analysis identified the reactivity for complement proteins (C3, factor B, C1q), activation products (C3b, iC3b, C4d, terminal complement complex), and regulators (factor H, C1-inhibitor, clusterin) within and around MS lesions even in the absence of evident ongoing inflammation (56). Complement staining was also present in normal-appearing white matter (NAWM) and cortex of MS patients, albeit to a lesser extent than in MS plaques, indicating its persistent local synthesis, activation, and regulation. Reactive astrocytes, frequently adjoining to both microglia clusters and damaged myelin/axons, were largely positive for cellular complement staining. This suggests a role of complement in the pathogenesis of cell, axon, and myelin damage.

As a part of innate immunity, platelets play a relevant role in MS pathogenesis (58–62). They increase both BBB permeability and CNS inflammation by either releasing proinflammatory mediators (matrix metalloproteinases, chemokines, and adhesion molecules), displaying inflammatory molecules on their surface, or interacting with endothelial cells and leukocytes, thus, triggering the latter to infiltrate the CNS (63). Alpha-granules are the most abundant platelet secretory granules. They contain numerous soluble factors involved in coagulation such as prothrombin, TF, high molecular weight kininogen, chemokines, proangiogenic and antiangiogenic proteins, growth factors, vWF, fibrinogen, and inhibitory proteases including antithrombin III, protein S, plasminogen, and TF pathway inhibitor.

Platelets participate in the acute phase of the inflammatory response in MS by producing significant amounts of IL-1alpha and other bioactive mediators that activate brain endothelium and promote the recruitment of leukocytes triggering and amplifying cerebrovascular inflammation and brain injury (64). Moreover, platelet-activating factor receptors are up-regulated in MS lesions, and abundant platelets have been shown within the CNS inflamed area of MS patients (62).

Through the production of ROS, activated platelets represent an additional source of oxidative stress for the CNS that has antioxidant mechanisms (65). Oxidative stress is dramatically increased during neuroinflammation, leading to damage of several cellular structures, particularly myelin.

Degenerative disorders, including MS, are associated with platelet dysregulation and excessive release of extracellular vesicles containing RNA and miRNA (short single-strand sequences of non-coding RNA) constituting approximately 70–90% of all vesicles circulating in the blood (66). Among nine exosomal miRNA profiles identified as promising candidate biomarkers to distinguish relapsing-remitting from progressive MS, two platelet-enriched miRNAs, miR-30b-5p and miR-223, are drivers of platelet production (67). Moreover, various platelet-related miRNAs have been found to be associated with both MS activity and duration, and the platelet-enriched geromiR miR-155 seems to be up-regulated in MS patients contributing to MS-associated inflammation and neurodegeneration (68).

Finally, in the experimental settings, platelets have been demonstrated to be a potential therapeutic target since platelet depletion ameliorates the EAE course (69).

Neuroimaging studies have been fundamental for providing a better insight into the pathophysiology of MS. In particular, studies using quantitative contrast-enhanced MRI showed a BBB leakage of small extent in non-enhancing MS lesions, which was not influenced by ongoing therapies and was different from an evident BBB damage of enhancing lesions, likely as a result of persisting reparative thickening of vessels within chronic MS lesions (70). These BBB abnormalities prevalently reflecting alterations of “tight” junctions (TJ) were demonstrated in NAWM (71) and even in the overall vascular CNS system, the latter probably due to the systemic effect of soluble pro-inflammatory mediators (72). It is not surprising that the chronic subtle BBB breakage can determine a persistent although soft discharge of inflammatory mediators and cells from blood to CNS with a slight but lasting fibrinogen leakage (73). Fibrinogen was found to be associated with both astrocyte processes and TJ abnormalities and correlated with diffuse microglial activation and weakened axonal and myelin integrity.

Moreover, dynamic-susceptibility contrast-enhanced (DSC) perfusion MRI showed delayed cerebral blood mean transit time (MTT) and reduced cerebral blood flow (CBF) in both NAWM and NA gray matter (NAGM) either in clinically isolated syndrome or in all forms of MS. These observations support a continuum of matter perfusion deceleration initiated in WM and spreading to GM (74–76). It is conceivable that the global hypoperfusion in GM and WM of MS patients may be determined by overall blood flow deceleration due to the inflammatory-thrombotic processes, which occur physiologically in the venous vessel bed, particularly during relapses frequently associated with the recurrent infections (77, 78).

Systemic infections can cause CNS damage so much so that peripheral inflammation resulted in being associated with disease exacerbations in experimental models of both MS and other neurodegenerative diseases (79, 80). Systemic immune activation influences local innate immunity, which, in turn, conditions adaptive immune response. During acute/subacute, thus delimited, CNS damage, neuroinflammation could be resolved and concluded with a regeneration area surrounding neurodegeneration (81). Conversely, chronic neuroinflammation inevitably leads to widespread neurodegeneration that, in the same way, spreads neuroinflammation and reduces CNS regenerative capacity. Natural regeneration in injured CNS tissue is insufficient in MS due to excessive extension of neuroinflammation and neurodegeneration.

Among the likely causes of acute and chronic neuroinflammation, there are recurrent and chronic infections accompanied by physiological immunothrombosis, as reported above (13). A continuous and close inter-correlated crosstalk between immune cells and coagulation is fundamental for an effective immune response aiming to restrain the dissemination of pathogens and to potentiate their elimination and tissue repair (12). Coagulation is activated during viral infections and plays multiple functions in the host immune system (82). The recent coronavirus (COVID-19) pandemic has confirmed a relevant role of coagulation activation during viral infection, especially in severe cases, with markedly elevated D-dimer and fibrin degradation product (83).

Temporal virus-BBB interlinkage during viral infections likely determines BBB breakdown triggering neuroinflammation and demyelination (84). A large Danish nationwide case-control study found that children who developed MS have had more infections than their peers 3 years prior, likely depending on their immune reaction to infections (85). Actually, some viruses have been identified to be responsible for the disease development by causing immune activation such as Epstein Barr virus, human herpesvirus 6, Torque teno virus, varicella zoster virus, poliovirus, Picornaviridae family including rhinovirus and enterovirus, coronavirus, adenovirus, influenza virus, and respiratory syncytial virus (86). For example, high anti-HHV-6 IgG titers indicative of HHV-6 infection as well as the immune response to HHV-6 antigens influenced the risk of MS relapses and likely MS progression (87).

Indeed, infections contribute not only to MS pathogenesis but also to disease exacerbation. It seems that about 30–40% of relapses occur after an upper-respiratory infection (88); these data are also confirmed by disease activity at MRI (89). Relapse rates are positively associated with upper-respiratory infections, and approximately two upper respiratory infections per year doubles the risk for MS relapse. After a peak in diagnosed influenza A cases in the general population, it was observed that the occurrence of MS relapse was 6.5 times more likely to occur (90).

In addition, a Cochrane review concluded that some pathogens such as human herpesvirus 6, Chlamydia pneumoniae, and Torque teno virus could contribute to MS progression (91). Therefore, not only viruses but also bacteria (e.g., *Chlamydia pneumonia*, *Staphylococcus aureus*, enterotoxin A) and fungal infections seem to have a role in both MS pathogenesis and course (92).

Altogether, these studies have pointed out the role of the coagulation pathway in close correlation with infections in the MS pathophysiology and its association with brain perfusion deceleration. This suggests possible therapeutic targets that may complement existing treatments. The aim of our study is to validate the pathogenetic role of coagulation together with brain hemodynamic abnormalities in MS.

